### Primary outcome measures

#### Anthropometry

Body weight and height are measured using an electronic scale to the nearest 0.1 kg and wall-mounted stadiometer to the nearest 0.1 cm, respectively. Waist and hip circumference are measured with a flexible tape to the nearest 0.1 cm. Hip circumference is measured a minimum of twice around the largest part of the buttocks. Waist circumference is measured a minimum of twice at the tip of the iliac crest. For both waist and hip circumference, an average is taken of the first two measures with internal variation of ≤ 1 cm.

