## Methods/design

### Research design

This study utilizes a single-arm, prospective design. Our goal is to recruit 40 overweight and obese patients (BMI for age > 85% WHO Growth Charts for Canada) between 7 and 17 years of age, who have an operated or non-operated CHD and reside in Southwestern Ontario. The underlying diagnoses include heart defects of mild and modest complexity, including atrial, ventricular, and atrio-ventricular septal defects, Tetralogy of Fallot, and coarctation of the aorta.

Eligible candidates are selected during patient visits and through chart review by a network of cardiologists at the London Health Sciences Centre (LHSC). Questions to confirm eligibility are also posed during recruitment by telephone. Consenting individuals undergo a physical assessment and review of medications and comorbidities during the first stage of their hospital visit for baseline measures. Incentives for participation include hospital parking, lunch vouchers, and reimbursement of transportation costs.

Exclusion criteria are inability to comply with research testing or intervention components due to mental and/or physical disabilities, medications or comorbidities affecting weight or metabolic condition, and involvement in any concurrent lifestyle intervention program. Parents and guardians are encouraged to be actively involved in their child’s program and to include all family members in making healthy lifestyle changes.

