#### Body composition measurements

A trained technician uses dual X-ray absorptiometry (iDXA; General Electric-Lunar iDXA, Ames Medical iDXA; Prodigy, enCORE 2007 software version 11.40.004, Waukesha, WI) to measure fat mass, lean mass, percent body and android fat, visceral adipose tissue, and bone mineral content. Lunar iDXA has been previously validated [23].

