### Sample size for the pilot and feasibility study and statistical analyses

A relatively small sample size (*n* = 40) was selected to test the feasibility of the intervention. A power calculation was not used as we were unable to determine the variability and expected difference in our primary outcome measures for our study population. As such, the results from the current study will provide the required information to perform power calculations for future studies.

The mean, SD, 80% confidence intervals, and 95% confidence intervals (95% CI) will be calculated and reported for all ratio and interval-based outcome measures, for each of the three time points and overall. The following hypothesis testing will also be performed, but purely as an exploratory exercise and as a component of the pilot. Temporal changes in primary and secondary outcome measures will be assessed using a repeated measures analysis of variance. Specifically, data will be analyzed using analysis of variance (ANOVA) and covariance (ACNOVA) with Bonferroni post hoc comparisons with IBM SPSS Statistics for Windows, version 24 (IBM, USA). Participants with missing data may be excluded from analysis if relevant. These data will be critical for informing future large-scale, controlled trials and establishing variances for the outcome metrics for sample size calculations.

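### Most named primary measures are absolute, growth-dependent quantities, so the exploratory one-year time tests in this single arm cannot separate expected growth from any programme effect

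*Protocol article*

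**What the plan says.** **Design.** Under Research design: "This study utilizes a single-arm, prospective design". Participants are "between 7 and 17 years of age" and are selected on BMI-for-age above the 85th percentile of the "WHO Growth Charts for Canada". This is the only growth-referenced quantity in the article, and it is an entry criterion. Outcomes are assessed at baseline, 6 months and 1 year.

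**Primary measures.** The domains are anthropometry, body composition and cardiorespiratory exercise capacity.
- Anthropometry: "Body weight and height are measured using an electronic scale" (to 0.1 kg) and a stadiometer (to 0.1 cm), plus waist and hip circumference to 0.1 cm.
- Body composition: DXA is used "to measure fat mass, lean mass, percent body and android fat, visceral adipose tissue, and bone mineral content".
- Fitness: peak VO2 from a maximal treadmill test, with no unit or scaling given.

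**Analysis.** "Temporal changes in primary and secondary outcome measures will be assessed using a repeated measures analysis of variance". ANOVA and ANCOVA with Bonferroni comparisons follow, and no covariate is named. Means and SDs are to be reported at each time point and overall. The same section calls the testing purely exploratory, and Research design says that the outcome measures are exploratory.

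**Use of the results.** The Background gives feasibility and impact as the objective. Selection of the most appropriate outcome measures says that the metrics serve to evaluate the intervention's impact. It bases a future sample size for each primary measure on the 80% upper confidence limit of its SD. Measures whose required sample size exceeds the median by 75% are to be re-evaluated.

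**The concern.** Children are selected on relative weight, but the anthropometry followed over the year is absolute weight and size. In growing children these quantities change whatever the programme does, and there is no control arm to show by how much.

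The direction differs by measure. Growth tends to raise weight, waist, fat mass and visceral fat, which can hide a fall in relative adiposity. It also tends to raise lean mass and bone mineral content (and peak VO2, if that is expressed in absolute units), which can look like benefit. Height is on the list, and its one-year change is essentially growth.

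Two outputs are exposed. One is the exploratory reading of impact. The other is the pilot's planning product: if the SD of a raw measure across ages 7-17 drives the future sample size, age spread enters that estimate and the rule that flags measures for re-evaluation.

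**Working it through.** **No plan figure to reproduce.** "A relatively small sample size (*n* = 40) was selected to test the feasibility of the intervention", and "A power calculation was not used as we were unable to determine the variability and expected difference in our primary outcome measures". The article gives no growth figures, so what follows is illustrative.

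**1. Which measures depend on growth, as listed**

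| Measure | Scale in the article |
|---|---|
| Weight, height, waist, hip | absolute |
| Fat mass, lean mass, visceral fat, bone mineral content | absolute |
| Percent body fat, percent android fat | size-normalised, though still dependent on age and puberty |
| Peak VO2 | not stated |

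**2. Would ANCOVA remove growth?** Not through a baseline covariate. Adjusting for baseline age explains why some children change more than others. The time effect evaluated at the mean age still contains the mean growth shift.

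**3. Growth-only rejection rate for raw weight**

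Inputs from the article: n = 40, and n = 28 at the 70% retention threshold (0.70 × 40 = 28). There are three time points, hence three pairwise contrasts and a Bonferroni level of 0.05/3 = 0.0167. Assumed: two-sided testing, growth-only 12-month gain m of 2-6 kg, SD of change s of 4-5 kg, programme effect zero.

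With d = m/s, the paired t statistic is non-central t with n − 1 degrees of freedom and non-centrality d√n. The two-sided critical value is 2.552 at n = 28 and 2.502 at n = 40. Example: m = 2, s = 5, n = 28 gives d = 0.40, non-centrality 0.40 × √28 = 2.12 and rejection probability 0.35.

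| Gain (kg) | s = 5, n = 28 | s = 5, n = 40 | s = 4, n = 28 | s = 4, n = 40 |
|---|---|---|---|---|
| 2 | 0.35 | 0.52 | 0.54 | 0.74 |
| 3 | 0.73 | 0.90 | 0.91 | 0.985 |
| 4 | 0.95 | 0.99 | 0.995 | 1.00 |
| 6 | 1.00 | 1.00 | 1.00 | 1.00 |

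For a smaller shift, d = 0.25, the probability is 0.13 (n = 28) or 0.19 (n = 40). A simulated three-time-point repeated measures ANOVA with linear growth (overall test at 0.05, 2,000 runs) rejects in 0.20 and 0.25 of runs at d = 0.25, in 0.62 and 0.79 at d = 0.5, and in 0.95 and 0.99 at d = 0.75 (n = 28 and n = 40).

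**4. After standardising.** If the reference fits, the expected growth-only change is about 0. The rejection rate then returns to 0.0167 for the Bonferroni contrast and about 0.044 in the simulated ANOVA.

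**5. Effect on future sample sizes, if the SD is cross-sectional.** Assume an age slope r of 0.1-0.5 residual SD per year and an age SD of 2.0-2.89 years (the upper value is a uniform spread over 7-17: 10/√12). For a fixed target difference, required n is proportional to the variance, which is inflated by 1 + (r × age SD)²:
- low end: 1 + (0.1 × 2.0)² = 1.04
- middle: 1 + (0.25 × 2.5)² = 1.39
- high end: 1 + (0.5 × 2.89)² = 3.09

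The 80% upper-limit factor on the SD comes on top: √(39/31.44) = 1.11 at n = 40 and √(27/20.70) = 1.14 at n = 28. The flagging rule cuts at 1.75 times the median sample size. Towards the upper end, age spread alone could carry an otherwise typical raw measure past that cut, provided the measures around the median are not inflated alike.

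**The case against.** **The sections describe instruments, not analysis variables.** Weight and height could simply be inputs to BMI-for-age, and a condensed article may leave derived indices to the full protocol or analysis plan. This has weight for the scaling of peak VO2 and for the covariates, whose absence is not criticised here. It does not dispose of anthropometry and absolute body composition, because the article lists those measures under a primary heading and names the test applied to their change.

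**Not every measure is raw.** Correct: percent body and android fat are already size-normalised, and the article never says that VO2 is absolute.

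**The tests are exploratory.** A reader might infer that growth will be reported as an effect, or a failure, of the programme. The documents do not support that. Research design and the analysis section both declare exploratory status, the analysis section looks ahead to controlled trials, and no feasibility threshold uses the significance of a time effect. If weight truly rises, rejecting no change is a correct statement about change, and the error would lie only in attributing it. What survives is that the article also states an aim of examining impact, and even an exploratory estimate needs an interpretable quantity.

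**The numbers are assumed and cover only raw weight.** True. They show sensitivity and do not predict results.

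**Standardising does not supply a control.** Also true: regression to the mean and secular change remain. The single-arm design is declared and is not itself an error.

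**Conclusion.** The point holds in limited form. Followed as written, the time effect for weight, height, waist, hip and the absolute DXA masses mixes expected growth with any programme effect, and baseline covariates would not undo this. Percent body and android fat are exceptions, and nothing can be said about peak VO2 beyond its unstated scaling.

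For raw weight the growth-only rejection probability runs from about 0.35 to 1.0, resting wholly on the assumed 2-6 kg gain and SD of change of 4-5 kg. The possible inflation of future sample sizes, 1.04- to 3.1-fold, rests on assumed age slopes and applies only if cross-sectional SDs of raw measures are used. The article does not say whether the SD is of levels or of change.

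No stated figure is wrong. Because the tests are exploratory and no feasibility criterion depends on them, this is a worthwhile, nearly costless improvement and not a flaw that invalidates the pilot.

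**What to change.** 1. Make WHO BMI-for-age z-score, on the reference already used for eligibility, the primary anthropometric measure.
2. Accompany it with waist-to-height ratio, fat mass index (fat mass divided by height squared) and the percent fat already listed.
3. State a size scaling for peak VO2.
4. Report raw weight, height, lean mass and bone mineral content descriptively.
5. Base the SDs in Selection of the most appropriate outcome measures and Sample size estimates on the standardised measures.
6. State that single-arm change is uncontrolled description: standardising removes expected growth only, not regression to the mean or secular change.

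The cost is wording and a little extra analysis. Height, weight, waist and DXA are already scheduled at all three assessments, so no new data collection is needed.

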#### Body composition measurements

A trained technician uses dual X-ray absorptiometry (iDXA; General Electric-Lunar iDXA, Ames Medical iDXA; Prodigy, enCORE 2007 software version 11.40.004, Waukesha, WI) to measure fat mass, lean mass, percent body and android fat, visceral adipose tissue, and bone mineral content. Lunar iDXA has been previously validated [23].

#### Cardiorespiratory exercise capacity

Breath-by-breath data on the volume of oxygen uptake (VO_2_) and carbon dioxide production are collected during a maximal exercise graded treadmill test using a Cosmed Quark b^2^ indirect calorimetry metabolic system (Cosmed S.r.I, Rome, Italy). An electrocardiogram is simultaneously used to monitor heart rate. The goal is to determine the peak VO_2_ based on the respiratory exchange ratio (*R*) ≥ 1.05 [24].

### Secondary outcome measures

#### Nutrition

Participants complete 3-day food records, which are reviewed through a single, multi-question pass by a registered dietitian. Recipes and brand names are collected when possible. Portion estimation, rather than weighed portions, is used to limit respondent burden. Thorough instructions and a portion estimation guide are provided in advance. The registered dietitian manually tabulates average intake from four Canadian food groups (servings of vegetables and fruit, grain products, milk and alternatives, and meat and alternatives) and fluid. Average caloric intakes are estimated for total energy, calories from “other foods” (e.g., candy, snack foods, and condiments), and calories from “sugar-sweetened beverages.”

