#### Program staff

Nutrition and physical activity counseling are provided by a registered dietitian and fitness specialist, respectively. The investigating cardiologists supervise the exercise stress tests and perform the tilt table echocardiography. Designated clinic technologists and nurses perform the various medical procedures in hospital (i.e., electrocardiography [ECG], echocardiography, blood work) with the assistance of regular clinic administrative staff. Research blood work is analyzed at the Translational Research Centre lab at LHSC. A trained research assistant guides participants through procedures and performs additional tests, such as peripheral arterial tomography (PAT) and jumping plate assessments. This pilot study also collaborates with designated individuals for dual-energy X-ray absorptiometry (DXA), exercise stress testing, spirometry, accelerometry, and waist and hip circumference measures. A research coordinator assists with program administrative duties and data management. Program software was developed in collaboration with Department of Electrical and Computer Engineering at UWO.

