#### Lifestyle intervention

During the initial hospital visit, participants are provided with a complimentary smartphone and one-year mobile plan. Participants without Wi-Fi at home are also given a limited data plan. The structured lifestyle intervention involves alternating weekly phone calls with two health coaches: a registered dietitian and a fitness specialist. A total of 50 phone calls (25 nutrition-related and 25 physical activity-related) are delivered over the one-year study. Phone counseling sessions are up to 30 min in duration. The duration of the call depends on the depth of material being covered and participant engagement. The phone calls are prescheduled for the year, taking place at a consistent evening time and day of the week. However, participants and coaches are encouraged to reschedule calls as needed between themselves. When appropriate, weekly counseling sessions are supplemented with relevant resources that are provided to patients via email or regular mail. After 6 months in the program, participants are introduced to supporting program-specific software that they can access online, as an additional way to interact with the program, set goals, and record their progress.

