### Nutrition counseling

Client and family-centered nutrition counseling includes an initial nutrition assessment and 24 subsequent conversations (i.e., phone calls) using motivational interviewing techniques intended to increase nutrition knowledge or skills and improve nutrition and eating behaviors. Standard nutrition education is provided, as deemed beneficial by the coach and participant (Table 1). If a participant has a particular nutrition concern or interest (e.g., lactose intolerance, sports nutrition), this education is also provided. Participants are encouraged to set SMART goals at the end of each session, which are followed up 2 weeks later. Nutrition and eating behavior is re-evaluated on a regular basis through 3-day food records obtained at baseline, 6 and 12 months, and supplemented with 24-h diet recalls by phone at 3 and 9 months. In the latter half of the program, participants are provided with optional family nutrition challenges (monthly) and eating behavior questionnaires (4 in total) to stimulate further family engagement and self-monitoring behaviors.

**Table 1 Tab1:** Nutrition and fitness program topics typically covered by time period for each participant

Time period	Program topics	
	Nutrition	Physical activity
Part 1: 0–6 months	Canada’s Food Guide, balanced meals, moderation, the division of responsibility in feeding, meal planning, healthier meal and drink ideas, grocery shopping, eating out, healthy drinks, label reading. *Family engagement*: bi-weekly resources *Evaluation*: Every 3 months (food records or diet recall)	Canada’s Physical Activity and Sedentary Behavior Guidelines, benefits of physical activity, sedentary behavior, interconnection of lifestyle behaviors and environment (sleep, activity, school), behavior change strategies. *Evaluation*: bi-weekly (physical activity recall)
Part 2: 6–12 months *Daily use of program-specific Internet-based application recommended*	Packing lunches, focused eating (satiety cues, emotional eating), eating out, sugar-sweetened drinks, family meals, eating breakfast, meal planning, label reading, increasing vegetables and fruit *Family engagement*: Monthly nutrition challenges *Evaluation*: every 3 months (food records or diet recall), eating habits questionnaires (4 in total)	Challenging current physical activity levels and diversity of movement choices, sustaining motivation levels and incorporation of rewards. *Evaluation*: bi-weekly (physical activity recall)

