## Discussion

In summary, this article has provided a rationale for the development of the intervention and an explanation of its study design and methods. This article has presented all of the information needed to develop and deliver a similar lifestyle intervention program, including making use of mobile technology as well as the study design, intervention components, and recruitment and measurement procedures. Although this feasibility study is ongoing, with an estimated completion date of the end of 2017, anecdotal reports from children and parents have been largely positive.

Despite the high completion rates, owing to the minimal burden on participating families, the following challenges were identified for future consideration of similarly designed studies: study compliance, technology, and measuring fitness and nutrition behavior.

The study is designed to mitigate certain potential compliance issues. First, adherence to the weekly telephone sessions may be challenging. For this reason, participants receive reminder text messages prior to their scheduled appointment times, which are rescheduled when necessary. The online supporting software may also be underutilized. To minimize this, participants are provided with in-person instruction on the software and are reminded to use the software through text messages and during counseling sessions.

The development of the online software required significantly more time than was originally planned, due, in part, to privacy reviews requested by the institutional REB. Researchers should temporally budget for software development and include respective institutional and governing research bodies early in the design process.

Quantifying physical activity is difficult because it is a multidimensional behavior; calculating the intensity, duration, frequency, and type with an all-encompassing tool is a challenge. Thus, accelerometers were chosen as an objective method of characterizing physical activity for this research project. Similarly, a variety of subjective and objective methods exist to characterize nutrition behavior. In this case, 3-day food records were chosen as the best approach to collect a variety of information about current participant intake and eating habits (e.g., timing of eating episodes, portion sizes, breakfast habits), which is useful for immediate interpretation by the registered dietitian in providing ongoing guidance to participants, with minimal participant burden.

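### The 3-day food record is both a coaching tool and a secondary outcome, apparently hand-scored by the coaching dietitian, so reporting and scoring drift cannot be told apart from dietary change

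*Protocol article*

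**What the plan says.** All references are to the protocol article.

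- **Source of the outcome.** Secondary outcome measures, Nutrition: "Participants complete 3-day food records, which are reviewed through a single, multi-question pass by a registered dietitian". On portions: "Portion estimation, rather than weighed portions, is used to limit respondent burden".
- **Who scores.** Same section: "The registered dietitian manually tabulates average intake from four Canadian food groups". Fluid belongs to the same tabulation. Calories (total, other foods, sugar-sweetened drinks) come in a separate sentence that says they are estimated but not by whom or how.
- **Who coaches.** Program staff: "Nutrition and physical activity counseling are provided by a registered dietitian and fitness specialist, respectively". Lifestyle intervention describes "alternating weekly phone calls with two health coaches: a registered dietitian and a fitness specialist", with 25 of the 50 calls on nutrition.
- **Use of the record in coaching.** Nutrition counseling lists, as part of the programme's regular re-evaluation, "3-day food records obtained at baseline, 6 and 12 months, and supplemented with 24-h diet recalls by phone at 3 and 9 months". The Discussion calls the record "useful for immediate interpretation by the registered dietitian in providing ongoing guidance to participants, with minimal participant burden".
- **Design and status.** Research design gives a single arm, makes nutrition a secondary metric and calls the outcome measures exploratory. The statistical analyses section tests change over time in primary and secondary outcomes, as an exploratory exercise only.

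**The concern.** The child reports intake to the person who appears to set and follow up the child's dietary goals. That person then questions the child about the record and converts estimated portions into servings. The behaviours measured overlap with those coached. Table 1 lists sugar-sweetened drinks and eating more vegetables and fruit as topics, and the web application (Table 2) has the child log treats and vegetable and fruit servings for the coaches to follow.

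Two kinds of drift can follow. The child may come to report in line with the advice, and the scorer, knowing the visit and the goals, may settle doubtful portions in line with expectation. Either would appear as a change in intake between baseline, 6 and 12 months. With no control arm, nothing can be subtracted.

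At stake is whether a reported improvement in diet can be read as one. Influence on nutrition-related outcomes is part of the study's aim as the abstract gives it.

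**Working it through.** The plan has no figure to reproduce: 40 was chosen without a power calculation. The check is mainly textual, followed by one illustration on assumed values.

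**1. Is the scorer the coach?**
- Nutrition gives the review and the serving tabulation to a registered dietitian.
- Program staff and Lifestyle intervention name one dietitian role, the coach. Program staff also lists collaborators for DXA, exercise testing, spirometry, accelerometry and circumferences, but no dietary assessor.
- The Discussion has the dietitian interpret the record at once to guide the participant.

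Together these make it a strong inference that one role does both. It is not stated outright.

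**2. Does the scorer know the visit?** This is not stated. It follows if the record is tabulated by the dietitian who uses it at once in coaching.

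**3. Which variables are affected?** Hand tabulation is tied to food-group servings and fluid. For calories no agent is named, so scorer bias there is possible but not shown. Bias in the child's reporting can affect both.

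**4. Would the feasibility criteria catch it?** Self-reports and questionnaires judges these instruments by compliance (at least 80% overall) and comprehension. A complete but biased record would pass.

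**5. Illustration of what a shift could do.** Assume no true change and a reporting or scoring shift of b SDs of the change score. For a two-sided paired t-test on n children, T is noncentral t with n − 1 degrees of freedom and noncentrality b√n, and the rejection probability is P(|T| > critical value). For example, b = 0.2 and n = 40 give 0.2 × √40 = 1.265.

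| Assumed b | n = 40, alpha 0.05 | n = 28, alpha 0.05 | n = 40, Bonferroni for 3 comparisons |
|---|---|---|---|
| 0.1 | 9.5% | 8.0% | 3.9% |
| 0.2 | 23.5% | 17.5% | 12.0% |
| 0.3 | 45.7% | 33.4% | 28.6% |
| 0.5 | 86.9% | 72.3% | 74.3% |

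Here 28 = 0.70 × 40, the minimum acceptable retention. The Bonferroni nominal level is 0.05 / 3 = 1.7% for each of the three pairs of visits.

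**6. Illustration in kcal.** Assume a true intake of 2,000 kcal/day and under-reporting that grows by 5 to 20 percentage points over the year. The false fall is 2,000 × 0.05 = 100 to 2,000 × 0.20 = 400 kcal/day. This only restates its assumptions and is no estimate for this study.

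**7. Workload of re-tabulation.** 40 children × 3 visits = at most 120 records.

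**The case against.** The case on the other side has five parts.

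- **Low stakes.** Nutrition is secondary, the tests are exploratory, and the primary outcomes (anthropometry, DXA, peak VO2) are instrument measures. No efficacy claim on diet is planned, and the Discussion already names measuring nutrition behaviour as a challenge. This stands and limits the severity. The Discussion does not, however, mention reporting or scorer bias.
- **Direction unknown.** A reader might infer that the plan proves intake change to be biased toward benefit. It does not. Questioning may recover omitted foods, and teaching on portions and labels may raise reported intake. A favourable shift is the likelier direction, no more.
- **Hand-scored calories.** A reader might infer that the coach also assigns energy and sugary-drink calories by hand. The Nutrition section does not say so.
- **Sample sizes.** A reader might infer that the shift distorts the planned sample-size estimates. Sample size estimates uses the 80% upper confidence limit of the SD, and a shift in the mean does not by itself change an SD. The remark about an unknown expected difference, in the statistical analyses section, concerns the primary outcomes. This inference is not supported.
- **Missing detail.** Masked coding or plausibility checks may be in the full protocol, which is not shown, so their absence from the article is not itself the point. What the article does fix is who tabulates servings and that the same record serves coaching.

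**Conclusion.** The concern holds as a risk, not as a demonstrated bias. As described, the food record is both a coaching aid and an exploratory secondary outcome, and its scorer appears to be the coach, who would know the visit. Change in reported intake is therefore at high risk of reporting and scorer bias, probably favourable, and a single-arm design cannot separate this from dietary change.

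Sign and size cannot be established from the documents. Both illustrations rest on assumed shifts. They show only that a modest one, such as 0.2 SD, would raise rejection with no true change from 5% to 23.5% at n = 40, or from 1.7% to 12.0% after Bonferroni. The conclusion also assumes that coach and scorer are the same role, which the text strongly suggests but does not say.

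The point is worth acting on because the remedy is cheap and leaves the intervention alone. It does not threaten the primary outcomes or the feasibility criteria.

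**What to change.** 1. **Separate scoring from coaching.** Keep the immediate review for coaching. Take the outcome from one batch tabulation after the last visit, on copies with study ID and visit label removed, in random order, with a written serving-size key. Existing staff can do this, where possible not the child's own coach. State who estimates the calories and include them in the same batch. This removes scorer expectation only. The child's reporting and the earlier questioning are already in the record.
2. **Add a descriptive sensitivity analysis.** At each visit, report the ratio of reported to expected energy from the weight, height, age and DXA lean mass already collected, with the accelerometer data taken into account and the requirement equation fixed in advance. Show all records. Do not make the analysis depend on a plausibility cut-off, which could remove children who truly ate less. Do not automatically label a falling ratio as reporting change, since weight may rise in growing children whose diet has improved.
3. **State the limit.** Interpret change in intake in light of the ratio, and say that reporting change cannot be separated from dietary change without a control arm.

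Cost: staff time to tabulate at most 120 records once, one ratio from existing data, and possibly a less favourable dietary result. No visit, counselling call or participant burden changes.
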